## Methods

### Study Design

A non-randomized observational design will be used to determine if the BST protocols for BN and BED are associated with statistical improvement from baseline assessment through one-year post-treatment. Despite the presence of a control group would allow for greater reliability of research findings, the present represents the only treatment option. Still, assessment of outcomes under observational studies informs the extent to which an intervention does what is intended to do in routine circumstances – thus allowing the optimization of healthcare interventions in ecological settings.

The study was approved by the research ethics board of Hesed House. Psychotherapy service registered charity number: CHY 1678.

### Participants

Participants diagnosed with BN and BED who self-referred to a state community psychotherapy clinic in Dublin, Ireland will be consecutively screened for inclusion into the study. The inclusion criteria will consist of the following: (1) 18 to 65 years old, (2) a diagnosis of BN or BED according to the DSM-5 (American Psychiatric Association, 2013), and (3) providing written informed consent to participate in the study. Exclusion criteria for the participants from the study were: (1) visual impairment that makes it difficult to complete written questionnaires, (2) hearing or cognitive impairment that makes it difficult to receive psychotherapy, and (3) presentation of comorbid psychiatric disorders, including substance abuse (Keski-Rahkonen and Mustelin, 2016), that could bias the results of the study. Eligible patients will be invited to participate in the study and provided with detailed information about the research aims and procedures. Those who agree to participate and sign the informed consent form will be included in the study.

### Outcome Measure

The *Eating Disorder Examination Questionnaire 6.0* (EDE-Q 6.0) (Fairburn et al., 2008) will be used as a measure of eating disorder feature severity. The EDE-Q 6.0 is a 28-item self-report questionnaire based on the EDE interview (Fairburn and Beglin, 1994). The items assess the frequency of behaviors indicative of an eating disorder over a 28-day period. The test is scored on a 7-point scale from 0 to 6 and has four subscales (i.e., restraint; eating concern; shape concern and weight concern) as well as a global score. The EDE-Q 6.0 has generally demonstrated adequately reliability and validity for eating-related pathology and specific disordered eating behaviors (Mond et al., 2004).

### Procedure

The study was approved by the research ethics committee of the clinic. Screening for inclusion will be conducted for consecutive patients at admission to the clinic by a clinical psychologist and psychotherapist who will be involved in the study screening and data collection stages only. Patients who will be eligible to participate will be subsequently informed about the study and invited to take part in the study. After completing the pre-treatment assessment (baseline), patients will receive 45–50 min of BST face-to-face treatment every 2 weeks for BN or BED based on their diagnosis for an anticipated total of 8 to 10 sessions. Participants will be assessed using the outcome measure (EDE-Q) at pre-treatment (T1), post-treatment (T2; approximately 16–20 weeks after the pre-treatment assessment), 6-month follow-up (T3), and 1-year follow-up (T4). During the treatment stage (T1 and T2), assessment will be conducted in a dedicated room at the clinic, whereas follow-up assessment (T3 and T4) will be conducted online.

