Cognitive behavioral therapy (CBT) is the most researched and recommended evidence-based treatment for BN and BED (Grilo, 2017). It aims to modify distorted beliefs about body image and alter the behaviors that are associated with and perpetuate EDs (Fairburn et al., 1993). Despite the widespread support for the efficacy of CBT (Murphy et al., 2010; Agras et al., 2017; Linardon and Brennan, 2017), a recent meta-analysis indicated that results are mixed (Linardon et al., 2017), and a significant proportion of people with BN or BED – particularly those with comorbid personality disorders (Grilo et al., 2007; Sallet et al., 2010; Farstad et al., 2016; Simpson et al., 2018) – have also been found to fail to respond to or not to complete CBT treatment (Waller et al., 2009).

In an effort to improve the quality and generalizability of BN and BED clinical treatment outcomes, the implementation of alternative treatments to CBT in non-research settings, and the evaluation of long-term treatment efficacy through the collection of follow-up data are needed (Tolin et al., 2015). Empirical investigations have shown brief strategic therapy (BST) to be clinically effective in treating several psychiatric disorders, and the results of recent experimental research have been encouraging enough in confirming its statistical efficacy and effectiveness to merit further investigation (Nardone and Portelli, 2005; Castelnuovo et al., 2011; Pietrabissa et al., 2016, 2017; Jackson et al., 2018).

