In the initial stage of the first three classes of BST treatment for BN, it is crucial to establish a therapeutic alliance, engage the patients, and bypass resistance to change (Nardone and Brook Barbieri, 2010). Individuals with BN are, in fact, collaborative in their intentions, but are also hindered by the fact that they rely on their strength of will. Depending on the patients’ perceptive-reactive system – the therapist may either use the *miracle fantasy* technique (i.e., What would need to happen in your life for you to be able to say, “My problem has been resolved?”) – to induce a form of positive self-deception by building a sort of prophecy that enables clients to form a strong image of a possible life without the problem – or ask the patients to think how to voluntarily worst their situation (*how worst* technique). This results in the recognition that the behaviors designed to protect them from binging are instead high-risk maintaining factors.

Further, family members are prescribed the *conspiracy of silence* (i.e., avoid talking about or acting on the problem) to interrupt attempted solutions who may be unwittingly colluding with keeping the current eating system intact (Nardone, 2003).

In the second stage of BST treatment for BN, the primary intervention is the *paradoxical diet* in which the individual is asked to think of what they would like to eat the most and carefully prepare and eat as much of those things as they want during mealtimes. The paradoxical logic underpinning the intervention is that “the only way to get rid of temptation is to yield to it” (Wilde, 1890), thus reducing the frequency of eating in favor of the pleasure of eating, and indirectly diminishing the daily amount of food the individual consumes (Nardone and Brook Barbieri, 2010). The paradoxical diet is usually accompanied by the *if you do once you do five* paradoxical prescription (i.e., From now until the next time we see each other, every time you eat something out of your three daily meals, you will have to eat it no more and no less than five times). It is aimed at transforming the guilty pleasure of eating outside of mealtimes into torture provoking extinction (Nardone et al., 1999). The concomitant usage of these two paradoxical prescriptions usually leads to a complete unblocking of the bulimic symptomatology in a few sessions.

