### Sample Size

The minimum sample size required to conduct this study was computed by using an *a priori sample size calculator* (G^∗^Power 3.1.9.2 software (Faul et al., 2007, 2009) for Fisher *f*’s tests. Participants – both BN than BED – will be measured with the EDE-Q 6.0 (Fairburn et al., 2008) at four time points: (1) at admission to the clinic, (2) at discharge, (3) at 6-month follow-up, and (4) at one year follow-up. *Clinical diagnosis* (BN *vs.* BED) was classified as between-group variable, and *time* was classified as within-subject variable. The *a priori* statistics (partial η^2^ and correlation between measures) were derived by considering previous longitudinal studies using the EDE-Q 6.0 (Fairburn et al., 2008) as measure of the range and severity of eating disorders’ features. The *a priori* partial η^2^ was set to assume a value of 0.020 (Fairburn et al., 2009) – small effect size (Cohen, 1988; Eid et al., 2017) – that provides a Cohen’s *f* equal to 0.143. Moreover, the Type I error (α) rate was set at 0.05 (two-sided) and the Power (1 – β) was set at 0.80, according to general guidelines (Cohen, 1988). In line with previous studies, the *a priori* correlation between repeated measures was set at 0.60 (Bardone-Cone and Boyd, 2007; Rose et al., 2013). Finally, sphericity was assumed. Results showed that there is an almost 81% chance of correctly rejecting the null hypothesis of no significant effect of the interaction with 28 subjects per group for a total of 56 participants.

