### Statistical Analysis

Data analyses will be performed using the R software (R Core Team, 2014), and lme4 package (Bates et al., 2015). First, preliminary analyses will be performed to test the assumptions of parametric statistics: if (strong) violations are detected, robust methods or data transformation will be applied. The EDE-Q 6.0 will be examined with the intention-to treat (ITT) analyses approach, with missing data replaced by baseline observations carried forward (BOCF) or last observation carried forward (LOCF), assuming no improvement for non-responders, as reported in previous studies (Castelnuovo et al., 2011). Dropouts will be excluded from the study.

The independent samples *t*-test will be used to examine between-group differences (BN *vs*. BED) in the EDE-Q 6.0 variables at all time-points, with attention to changes in the scores. The chi-square statistic will be used to test the association between treatment groups and socio-demographic variables (gender, age, marital status and employment status), and correlation analysis will be used to test the association between quantitative variables. Finally, multilevel growth curve model analysis will be used to estimate the average growth trajectories from baseline to one year after treatment for the EDE-Q 6.0 scores with corrected effect sizes (Hedges’ *g*) and 95% confidence interval.

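### No EDE-Q is scheduled during therapy and dropouts are to be excluded, so early leavers may contribute only a baseline score or nothing, and the one-year change is biased if leaving follows early response

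*Protocol article*

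**What the plan says.** The Procedure section states "Participants will be assessed using the outcome measure (EDE-Q) at pre-treatment (T1), post-treatment (T2; approximately 16–20 weeks after the pre-treatment assessment", followed by 6-month (T3) and 1-year (T4) follow-up. The Sample Size section lists the same four occasions: "1) at admission to the clinic, (2) at discharge, (3) at 6-month follow-up, and (4) at one year follow-up". Therapy is given "every 2 weeks for BN or BED based on their diagnosis for an anticipated total of 8 to 10 sessions". Patients are therefore in the clinic every fortnight, but no EDE-Q is listed between T1 and T2. T1 and T2 are completed at the clinic, "whereas follow-up assessment (T3 and T4) will be conducted online".

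The Statistical Analysis section promises an intention-to-treat analysis "with missing data replaced by baseline observations carried forward (BOCF) or last observation carried forward (LOCF"), on the assumption that non-responders do not improve. It then says that dropouts will be left out of the study. A multilevel growth curve model is to estimate the trajectory from baseline to one year after treatment. The article gives no expected dropout rate. It does not say whether T2, T3 or T4 will be sought from a patient who stops therapy.

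**The concern.** Take a patient who stops after a few sessions and gives no later score. Only T1 is on record. Last observation and baseline observation are then the same number, so the open choice between the two carry-forward rules makes no difference and the patient's change is set to zero. Under the exclusion sentence the patient is removed altogether. If the patient stays in the growth model unimputed, the model knows the starting severity but nothing about the response to therapy before leaving.

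That response may well drive leaving. The Introduction says that a significant proportion of people with BN or BED "have also been found to fail to respond to or not to complete CBT treatment". The account of the BN protocol says that two of its prescriptions together "usually leads to a complete unblocking of the bulimic symptomatology in a few sessions". On the article's own view, informative change can come early, while patients still attend, and it is not recorded.

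The study has no control group. The within-patient change from baseline is the evidence of efficacy, and no comparison arm can offset a bias in it.

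**Working it through.** **The plan's own figures.** The article gives no figure for this bias. It supplies the correlation between repeated measures (0.60) and the sample size (56). Its power statement reproduces: f = √(0.02/0.98) = 0.1429; λ = 56 × 4 × 0.1429² / (1 − 0.60) = 11.43; with 3 and 162 degrees of freedom at α = 0.05, power is 81.0%, against the stated value of almost 81%. That calculation treats all 56 patients as analysed.

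**Simulation.**
- From the article: correlation 0.60, taken as equal between all pairs of occasions.
- Assumed: scores in SD units; means 0, −0.6, −1, −1, −1 at T1, mid-treatment, T2, T3 and T4, so the true one-year fall is 1.0 SD.
- Assumed: logit of leaving = a + b × (change from T1 to mid-treatment + 0.6), with a = −1.5 or −1.0 and b from 1 to 2. This gives 21–34% leaving, more often after a poor early response. Leavers give no T2, T3 or T4.
- The likelihood model has unstructured means and covariance, as a stand-in for the planned growth curve.

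| Analysis | Estimated fall (SD) | Error |
|---|---|---|
| Completers only | 1.08 to 1.18 | 8–18% too large |
| Baseline carried forward (identical to LOCF here) | 0.78 to 0.85 | 15–22% too small |
| Likelihood model, T1–T4 | 1.05 to 1.12 | 5–12% too large |
| Same model plus one mid-treatment score | 1.00 | none |

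**How the answer depends on the mechanism.**
- Leaving unrelated to anything (b = 0): completers and the T1–T4 model are unbiased. Carry-forward still shrinks the fall, to (1 − d) × 1.0 SD for a proportion d leaving.
- Leaving depends on baseline only, 10–40% leaving: the T1–T4 model gives 1.00 at every rate, and carry-forward gives 0.86 down to 0.50.
- Leaving depends on the level of the mid-treatment score rather than on the change, 10–40% leaving: the T1–T4 model gives 1.03 to 1.11, and 1.00 with the mid-treatment score. Completers give 1.00, because a mid-treatment score equally correlated with T1 and T4 shifts both alike.
- Leaving depends on the unseen T2 level, 10–40% leaving: the model gives 1.03 to 1.11 without the mid-treatment score and 1.02 to 1.07 with it.
- Leaving depends on the unseen change to T2: in one case 1.116 falls to 1.075, so the added score removes (0.116 − 0.075)/0.116 = 35% of the bias.

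**Timing of an added score.** With sessions 2 weeks apart, the fifth falls 4 × 2 = 8 weeks (56 days) after the first. The questionnaire covers 28 days, so its window runs from day 28 to day 56 and lies wholly within treatment.

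**The case against.** A reader might infer that every early leaver necessarily has a baseline score and nothing else. The article does not say so. T2 is also described as the discharge assessment, and T3 and T4 are online, so a leaver could still supply the one-year score. The text that removes leavers is the exclusion sentence in Statistical Analysis, not the visit schedule. This stands, which is why the point is worded as what may happen, and why the analysis rule is the first thing to change.

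A reader might also infer that no growth model could recover the one-year effect. That is too strong: a likelihood model on unimputed scores recovers it when leaving is random or depends on baseline.

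Nor does an added visit cure the problem alone. While dropouts are excluded, a leaver's mid-treatment score would be discarded, and its value depends on replacing carry-forward. The full recovery to 1.00 arises where leaving depends on exactly what the added score measures or is predicted by it.

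Other objections carry weight:
- **Size.** With correlation 0.60 and all 56 patients, the standard error of the T1–T4 change is √(2 × 0.40/56) = 0.12 SD. The model's bias of 0.05 to 0.12 SD is at or below one standard error. A larger sample would not remove it, but it is not dramatic here.
- **Supporting text.** The statement about non-completion concerns CBT, and particularly patients with comorbid personality disorders, whereas this study excludes comorbid disorders that could bias results. The statement about rapid change concerns two prescriptions for three of the four BN types, not the vomiting type or BED. Both make response-related leaving plausible; neither shows that it will occur.
- **Fit to the aim.** Pre, post, 6-month and 1-year scores do match the stated aim. Four occasions are a legitimate choice, and the case for a fifth is its low cost.

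**Conclusion.** The point holds in a limited form. No EDE-Q is scheduled during therapy, and the plan both carries values forward and excludes dropouts. Early leavers may therefore enter with a baseline score only, or not at all. If leaving is related to early response, the direction of the error turns on which sentence of the plan is followed: about 15–22% too small under baseline carried forward, and about 8–18% too large in completers when leaving tracks early change. Keeping leavers in a likelihood model on T1–T4 reduces the error to 5–12% too large but does not remove it.

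These sizes rest on assumed dropout of 21–34%, an assumed trajectory and an assumed reason for leaving. They show direction and order of magnitude; they do not predict this study's bias. The documents do not support the stronger claims that leavers cannot be followed up or that the growth model must fail. This is a cheap improvement, best settled before data collection because an early score cannot be supplied afterwards.

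**What to change.** In Statistical Analysis, delete the exclusion of dropouts. Fit the multilevel model by maximum likelihood to all observed EDE-Q scores of every patient who started therapy, without carry-forward replacement. Keep BOCF or LOCF at most as a sensitivity analysis.

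In Procedure, state that T2, T3 and T4 will be sought from patients who stop therapy. Add one EDE-Q, completed in the clinic room at about the fifth session, and enter it in the model as a further time point. T1 to T4 and the baseline-to-one-year estimate stay as they are.

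The added score costs one 28-item self-report per patient at a session already scheduled, with no extra visit or staff. The downside is a few minutes of patient time and one more exposure to the questionnaire. It does nothing for patients who leave before that session, and it removes only about a third of the bias when leaving depends on later, unseen scores. Seeking T2–T4 after therapy stops complements it, but relies on the cooperation of patients who have left.

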### Psychotherapists and Treatment Fidelity

All psychotherapy sessions will be provided by two licensed brief strategic therapists with substantial experience in the treatment of BN and BED. To ensure treatment fidelity, therapy sessions will be video-recorded and randomly audited by two senior licensed BST psychotherapists. Only patients who agree to be video registered during the psychotherapy sessions will be included in the study.

### Sample Size

The minimum sample size required to conduct this study was computed by using an *a priori sample size calculator* (G^∗^Power 3.1.9.2 software (Faul et al., 2007, 2009) for Fisher *f*’s tests. Participants – both BN than BED – will be measured with the EDE-Q 6.0 (Fairburn et al., 2008) at four time points: (1) at admission to the clinic, (2) at discharge, (3) at 6-month follow-up, and (4) at one year follow-up. *Clinical diagnosis* (BN *vs.* BED) was classified as between-group variable, and *time* was classified as within-subject variable. The *a priori* statistics (partial η^2^ and correlation between measures) were derived by considering previous longitudinal studies using the EDE-Q 6.0 (Fairburn et al., 2008) as measure of the range and severity of eating disorders’ features. The *a priori* partial η^2^ was set to assume a value of 0.020 (Fairburn et al., 2009) – small effect size (Cohen, 1988; Eid et al., 2017) – that provides a Cohen’s *f* equal to 0.143. Moreover, the Type I error (α) rate was set at 0.05 (two-sided) and the Power (1 – β) was set at 0.80, according to general guidelines (Cohen, 1988). In line with previous studies, the *a priori* correlation between repeated measures was set at 0.60 (Bardone-Cone and Boyd, 2007; Rose et al., 2013). Finally, sphericity was assumed. Results showed that there is an almost 81% chance of correctly rejecting the null hypothesis of no significant effect of the interaction with 28 subjects per group for a total of 56 participants.

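### The stated 81% power counts the between-measure correlation twice; for a partial eta-squared of 0.020, power with 56 patients is about 29%

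*Protocol article*

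**What the plan says.** The Sample Size section describes an a priori G*Power calculation with diagnosis (BN or BED) as the between-group factor and time as the within-subject factor, measured "at four time points". The planning statistics "were derived by considering previous longitudinal studies using the EDE-Q 6.0". The partial eta-squared "was set to assume a value of 0.020", is described as a small effect, and is converted to a Cohen's f "equal to 0.143". The "correlation between repeated measures was set at 0.60", sphericity is assumed, alpha is 0.05, and target power "was set at 0.80, according to general guidelines". The result is that "there is an almost 81% chance of correctly rejecting the null hypothesis of no significant effect of the interaction with 28 subjects per group", 56 in total. The section does not name the G*Power effect-size option or mention any rescaling of f for the correlation.

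**The concern.** The same f can mean two things in a repeated-measures design. One version divides the effect by the total within-cell standard deviation; the other divides it by the within-subject error, which is smaller by the factor (1 − ρ). A partial eta-squared for an interaction with time is SS_effect / (SS_effect + SS_within-error), so an f derived from it is of the second kind. A formula that then divides by (1 − ρ) applies the gain from correlation again.

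This is the only power statement in the article and the sole basis for calling 56 the minimum sample. If it is wrong, a non-significant diagnosis-by-time result could be read as adequately powered evidence that BN and BED follow the same course, when the chance of missing the planned effect is about 70%.

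**Working it through.** **Inputs, all from the Sample Size section:** partial eta-squared 0.020; ρ = 0.60; m = 4 measurements; k = 2 groups; N = 56; sphericity (ε = 1); α = 0.05; tested effect, the group-by-time interaction.

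**Conversion.** f² = 0.020 / 0.980 = 0.020408, so f = 0.143, as printed.

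**Degrees of freedom.** (k − 1)(m − 1) = 3 and (N − k)(m − 1) = 54 × 3 = 162. The critical value is F = 2.660. Power comes from the noncentral F distribution with noncentrality λ.

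**1. The plan's own figure (default option, f on the total-SD scale).**
λ = f² · N · m / (1 − ρ) = 0.020408 × 56 × 4 / 0.4 = 11.43. Power = 81.0%.
With N = 54, power is 79.4%, so 56 is the smallest balanced total that reaches 80%. Both the 81% and the 56 reproduce, which identifies the calculation that was run.

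**2. The formulas that match a partial eta-squared.**

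| Definition | λ | Power at N = 56 | Total N for 80% |
|---|---|---|---|
| f² · (N − k) · (m − 1) (G*Power, as in SPSS) | 0.020408 × 54 × 3 = 3.31 | 29.4% | 182 |
| f² · N · (m − 1) (G*Power, as in Cohen) | 0.020408 × 56 × 3 = 3.43 | 30.4% | 180 |

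**3. Where the gap comes from.** The ratio of noncentralities is 11.43 / 3.43 = 3.33. Of this, 1 / (1 − 0.60) = 2.5 is the correlation applied a second time. The other factor, 4 / 3 = 1.33, comes from counting m rather than m − 1. To enter a partial eta-squared of 0.020 correctly in the default option, f² must first be multiplied by (m − 1)(1 − ρ) / m = 3 × 0.4 / 4 = 0.30. This gives f = √(0.020408 × 0.30) = 0.078 rather than 0.143, and power of 30.4%.

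**4. Simulation.** The interaction test was simulated with 28 per group, ρ = 0.60 and 20,000 runs. With the effect set to a partial eta-squared of 0.020, 30.7% of runs rejected. With f = 0.143 taken on the total-SD scale, 80.9% rejected.

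**5. What 56 patients can detect.** Power of 80% with 3 and 162 degrees of freedom needs λ = 11.17.
- First definition: f² = 11.17 / 162 = 0.0689, so partial eta-squared = 0.0689 / 1.0689 = 0.0645.
- Second definition: f² = 11.17 / 168 = 0.0665, so partial eta-squared = 0.0665 / 1.0665 = 0.062.

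**The case against.** The strongest reply is that 29% is conditional. The article does not say which effect in the cited work the 0.020 describes, and that work is not available here. If f = 0.143 was chosen directly as a conventional small effect relative to the total standard deviation, the 81% is correct. That is possible, but the text points the other way: it calls the quantity a partial eta-squared, says it was derived from longitudinal studies, and presents f as a conversion from it. Even on the favourable reading the paragraph mislabels its effect size and needs correcting.

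It can also be said that each arithmetic step is right and that a condensed article may omit the software option. Both are true. The fault, however, is not the omission: the printed effect size, correlation, sample size and power do not agree with one another.

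Further, the Study Aim concerns change over time, the Discussion states no hypothesis of a BN–BED difference, and the study is presented as hypothesis-generating. This limits the harm. It does not make the only stated justification for 56 patients correct.

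One objection stands in part. The 29% belongs to a 3-degree-of-freedom repeated-measures ANOVA with complete data, whereas the Statistical Analysis section plans a multilevel growth curve model. If the whole effect lay in a linear slope difference, a 1-degree-of-freedom test with the same λ of 3.31 would have about 43% power, still far below 81%. Any restated figure should name the test it refers to.

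**Conclusion.** The concern holds. The stated inputs do not deliver the stated power: for a partial eta-squared of 0.020, 56 patients give 29% to 30%, an overstatement of about 50 percentage points. Reaching 80% for that effect would take 180 to 182 patients, a little over three times the planned number.

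The conclusion rests on 0.020 being a repeated-measures partial eta-squared for the within-subject effect, and on the plan's own assumptions of ρ = 0.60, sphericity and no missing data. The 29% itself does not depend on ρ, because a partial eta-squared already absorbs it. The plan's formula, by contrast, moves from 40% at ρ = 0 to 91% at ρ = 0.7.

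**What to change.** Leave enrolment as it is and correct the Sample Size paragraph. Suggested wording:

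*With 28 patients per group, complete data and sphericity, the repeated-measures ANOVA test of the diagnosis-by-time interaction has about 80% power for a partial eta-squared of 0.065. For a partial eta-squared of 0.020 the power is about 29%.*

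Name the G*Power effect-size option used. The small-effect label may stay with 0.020 but should not describe what 56 patients can detect. If f = 0.143 was in fact intended relative to the total standard deviation, say so, justify it on that scale, and remove its derivation from a partial eta-squared.

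The cost is one reworded paragraph and a less favourable stated power. No study procedure changes.

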## Study Aim

The present study is designed to test the long-term efficacy of the BST treatment for BN and BED by assessing eating disorder symptomatology in a non-research outpatient clinic through one-year post-treatment.

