## Discussion

This paper provides a description of a proposal to evaluate the long-term efficacy of BST for the treatment of BN and BED in a real-world setting. Whilst the superiority of BST over CBT for the long-term treatment of BED has been shown in a previous study (Jackson et al., 2018), no research has yet investigated the long-term efficacy of BST for the treatment of BN. It is expected that findings will increase knowledge of the impact of BST for BED, while – for the first time – statistically testing the long-term effects of the BST protocol for BN. Due to its novelty, no hypothesis was made about the possible contribution of BST for the treatment of BN. Instead, it has been hypothesized that BST will promote sustained remission of BED symptoms.

Despite a few limitations – including the absence of a control group and the use of a single psychological measure – the research design is adapted to the clinical setting with the aim to move research into practice. Therefore, research findings will lack of generalizability, but will be useful to generate new formal hypotheses and to develop more precise research design in real-world settings.

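### The 56 patients are justified by power for a BN-versus-BED by time interaction, which does not test the stated aim of improvement to one year under BST

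*Protocol article*

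**What the plan says.** All references are to the protocol article.

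- **Aim.** Study Aim says the study is "designed to test the long-term efficacy of the BST treatment for BN and BED by assessing eating disorder symptomatology", through one year after treatment. Study Design makes this operational: the question is whether the BST protocols are "associated with statistical improvement from baseline assessment through one-year post-treatment". There is no control group.
- **Hypotheses.** The Discussion expects sustained remission in BED. For BN it says that "no hypothesis was made about the possible contribution of BST for the treatment of BN". No section states a hypothesis that BN and BED follow different courses.
- **Sample size.** Diagnosis (BN or BED) "was classified as between-group variable, and *time* was classified as within-subject variable". The EDE-Q is taken "at four time points: (1) at admission to the clinic, (2) at discharge, (3) at 6-month follow-up, and (4) at one year follow-up". With partial eta squared 0.020 (f = 0.143), alpha 0.05, correlation 0.60 and sphericity assumed, the section reports almost 81% power to reject "no significant effect of the interaction with 28 subjects per group for a total of 56 participants". It gives no power for the time effect, overall or within a diagnosis.
- **Analysis.** Statistical Analysis plans t-tests of BN against BED at each time point, and a multilevel growth curve model to "estimate the average growth trajectories from baseline to one year after treatment".

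**The concern.** The aim asks whether patients get better and stay better. The interaction asks whether BN and BED change differently. Since both groups receive BST, the interaction is not a treatment contrast, and its result does not settle the aim in either direction. A therapy that worked equally well and lastingly in both diagnoses would normally give a null result on the only test for which power is stated. Two groups moving in opposite directions could give a significant one.

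A reader will take the 81% as the chance of showing efficacy. The plan makes no such claim, and at the level where its one hypothesis sits (BED alone, 28 patients) the same inputs give a much lower figure.

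**Working it through.** **Inputs** (Sample Size): k = 2 groups, m = 4 measurements, N = 56, partial eta squared 0.020, correlation 0.60, alpha 0.05, sphericity.

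**1. The plan's own figure.** f = sqrt(0.02/0.98) = 0.143. Noncentrality = f² × N × m/(1 − 0.60) = 0.02041 × 56 × 4/0.40 = 11.43. Degrees of freedom are (k − 1)(m − 1) = 3 and (N − k)(m − 1) = 162. The noncentral F gives power 0.810. At N = 54 it is 0.794, so 56 is the smallest even total that reaches 80%. The stated figure is correct for the interaction.

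**2. Time effect pooled over both diagnoses, same inputs.** Noncentrality is again 11.43. The numerator df is m − 1 = 3, and the denominator df is 162. With two groups all three quantities equal those of the interaction, so power is the same 0.810.

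**3. Time effect within one diagnosis, n = 28.** Noncentrality = 0.02041 × 28 × 4/0.40 = 5.71, with df 3 and (28 − 1) × 3 = 81. Power is 0.476. Reaching 80% at this effect size would take 55 patients in that diagnosis. With 28, 80% is reached at f = 0.202.

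**4. The same N as a paired T1-to-T4 change.** SD of change = sqrt(2 × (1 − 0.60)) = 0.894 SD. For a two-sided paired t-test at 0.05:

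| | n | change with 80% power | 95% CI half-width |
|---|---|---|---|
| One diagnosis | 28 | 0.49 SD | 2.052 × sqrt(0.8/28) = 0.35 SD |
| Pooled | 56 | 0.34 SD | 2.004 × sqrt(0.8/56) = 0.24 SD |

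**5. How the plan's f compares.** If patients improve by d at T2 and hold it, the four means are 0, −d, −d, −d. Their standard deviation is d × sqrt(3)/4 = 0.433d, so f = 0.143 corresponds to d = 0.33 SD. A paired test on 28 patients has about 47% power for that change. This agrees with step 3. The drop-and-hold pattern is an assumption.

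**6. What the interaction test responds to.** Simulation with 28 per group, correlation 0.60 and 5000 runs; the mean patterns are illustrative and not from the article.

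| True means (SD units, T1 to T4) | interaction rejects | time effect rejects |
|---|---|---|
| Both groups 0, −0.8, −0.8, −0.8 | 4.8% | 100% |
| One group 0, −0.25, −0.25, −0.33; the other its mirror image | 67% | 5.0% |

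The first row is full success in both diagnoses, and the interaction rejects at about alpha. The second row has no average improvement, and the interaction rejects in two runs out of three.

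**The case against.** **The 81% may still be useful.** A reader might infer that 56 patients are too few for the aim, or that the 81% has no bearing on it. The article's inputs do not support that. Step 2 gives the same 81% for the pooled time effect at f = 0.143. Even within one diagnosis, 28 patients have 81% power for a 0.5 SD change and over 99% for 0.8 SD (illustrative values). This part of the objection stands: the gap is in which effect is named, and in power within a single diagnosis at the plan's own effect size.

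**Comparing BN with BED is a planned question.** The abstract describes a two-group study, the two diagnoses follow different BST protocols, and between-group t-tests are planned. Powering that comparison is therefore not arbitrary. It is still neither the stated aim nor a stated hypothesis. Nothing in the article says the interaction will be reported as evidence for or against BST, so misreading is a risk and not something the plan commits to.

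**The growth model.** A reader might infer that the model fits one straight line through therapy and follow-up, and so would confuse the treatment gain with its maintenance. The article does not say the trajectory is linear. Growth curve models can be piecewise or treat time as a factor, and that choice may be left to an analysis plan. No criticism of a linear slope is made here.

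**The study is modest in its claims.** The Discussion presents it as hypothesis-generating, and the model already comes with 95% confidence intervals. That limits the harm, but the sample-size paragraph still attaches its power to a test that does not answer the aim.

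**Conclusion.** The concern holds. The arithmetic in Sample Size is right, but the effect it powers does not test efficacy as Study Aim and Study Design define it. On the plan's own inputs, 56 patients give 81% power for the time effect pooled over both diagnoses and about 48% within one diagnosis, which is where the BED hypothesis lies. The article states neither figure.

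These results assume f = 0.143, correlation 0.60, sphericity, and all 28 patients per diagnosis analysed. The conclusion that the interaction is the wrong test for the aim depends on none of these numbers; it follows from both groups receiving BST.

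**What to change.** 1. **Primary contrast.** Name the T1-to-T4 change in EDE-Q global score, estimated from the multilevel model overall and for each diagnosis. Either identify BED as the confirmatory group, since it carries the only stated hypothesis, or give a multiplicity rule. The rule matters: testing each diagnosis at 0.025 lowers power for a 0.49 SD change with 28 patients from 80% to about 70%.
2. **Maintenance.** Report the T2-to-T4 change as the maintenance result.
3. **Interaction.** Make diagnosis-by-time secondary.
4. **Sample-size paragraph.** Restate it for N = 56: at f = 0.143 and correlation 0.60, power is 81% for the pooled time effect and about 48% within one diagnosis of 28. As a paired T1-to-T4 change, 80% power is reached at 0.34 SD pooled and 0.49 SD within a diagnosis (95% CI half-width 0.35 SD). Present the SD figures as what the sample can detect and how precise it is, not as targets chosen in advance, since the article contains no such targets.

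The cost is rewording and a less favourable stated power per diagnosis. No extra patients or data are needed for this restatement. If 80% power within a diagnosis at f = 0.143 were wanted, it would take about 55 patients in that diagnosis.
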